### Inclusion criteria

(1) Confirmed by MRI and meeting the diagnostic criteria for ischemic cerebrovascular disease; (2) Aged between 40 and 80 years, regardless of gender; (3) Insomnia first occurring more than 2 weeks after acute stroke, with no prior history of insomnia; (4) Pittsburgh Sleep Quality Index (PSQI) score > 7; (5) Conscious and able to cooperate with all scale assessments; (6) Voluntary participation in the study, signing the informed consent form, and committing not to participate in other clinical studies during the treatment period.

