### Interventions

In the taVNS group, a taVNS device will be used (Hwato, SDZ-IIB, Suzhou, China) to stimulate the auricular branch of the vagus nerve distribution area located posterior and inferior to the external auditory meatus, with clear anatomical localization. The stimulation parameters will be as follows (31, 32): (1) dense-sparse waves with a pulse frequency of 4/20 Hz; (2) current intensity of 3–14 mA, individually adjusted according to the patient’s tolerance; (3) stimulation time of 30 min per session. Patients will be placed in a comfortable position. The treatment will be administered once daily, five days per week, for a total of four weeks. These parameters were chosen on the basis of our team’s previous taVNS trials in primary insomnia and depression, in which the same dense-disperse 4/20 Hz waveform and 30-minute daily session produced clinical benefit with good safety and tolerability (15, 31, 32). The auricular branch of the vagus nerve distribution was selected as the stimulation target because this region is densely innervated by vagal afferent fibers, enabling direct, non-invasive activation of the vagal pathway. The current intensity will be individually titrated within the 3–14 mA range to the highest level that evokes a distinct but non-painful tingling sensation, so as to ensure adequate afferent activation while maintaining tolerability and minimizing the risk of adverse effects (10). The 4-week course was set to match the intervention duration shown to be effective in our prior insomnia studies and to align with the typical timescale of post-stroke neuroplastic change.

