### Basic treatment

During the 4-week intervention period, all participants will receive standard basic treatment, including conventional post-stroke medication and rehabilitation training. Medication will be administered in accordance with the *Chinese Guidelines for the Diagnosis and Treatment of Acute Ischemic Stroke 2023* (35). Rehabilitation training will include functional training, routine medical care, and other standard rehabilitation procedures.

To avoid potential confounding effects on sleep outcomes and multimodal MRI indicators, sedative-hypnotic drugs will not be routinely prescribed during the study period. Estazolam will be permitted only as rescue medication when participants experience severe or intolerable insomnia, such as inability to sleep for two consecutive nights or when clinically judged necessary by the investigator. The recommended rescue dose will be estazolam 1 mg orally before bedtime. The use of rescue medication, including dosage, frequency, and timing, will be recorded in detail throughout the study. Participants will be instructed to avoid taking estazolam within 48 hours before MRI scanning and clinical assessments whenever clinically feasible.

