### Outcome measures

#### Primary outcomes

The primary outcomes include neuroimaging indicators derived from fMRI, 3D-T1WI, and ASL, specifically: The primary outcome is defined as the change in these multimodal MRI indicators from baseline to the end of the 4-week intervention; the principal comparison is the between-group difference in these changes (taVNS vs. sham-taVNS), with within-group pre-to-post changes assessed as a secondary contrast. The specific indicators are as follows:

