### Data analysis

#### Imaging data analysis

The rs-fMRI data will be preprocessed using SPM12 (https://www.fil.ion.ucl.ac.uk/spm/) and DPARSF 5.0 toolkit (56) with Matlab 2020a. Data preprocessing includes the first ten time points removed to allow for magnetization equilibrium, slice timing correction, realignment for head motion correction (subjects with head motion exceeding 2 mm in translation or 2° in rotation will be excluded), spatial normalization to Montreal Neurological Institute (MNI) space and resampled at 3 mm × 3 mm × 3 mm voxel size, spatial smoothing with a 6 mm full-width at half maximum Gaussian kernel, linear detrending, nuisance covariates regression (including 24 head motion parameters, white matter signals, and CSF signals), and band-pass filtering (0.01–0.08 Hz).

After standard preprocessing, ReHo, ALFF, and fALFF analyses will be calculated to explore regional brain activity. For FC analysis, seed regions will be defined based on brain areas showing significant differences in ALFF, fALFF, or ReHo analyses, and the mean time series of each seed region will be correlated with the time series of all other voxels across the whole brain using Pearson’s correlation coefficients, which will be subsequently transformed to z-values using Fisher’s r-to-z transformation to improve normality (57). Two-sample Student’s t-tests and paired Student’s t-tests will be conducted respectively to examine the differences in taVNS-related central responses between groups and within groups. The results will be corrected by Gaussian Random Field (GRF) Theory (voxel-level *P* < 0.005, cluster-level *P* < 0.05) (58).

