ASL data processing will be performed using SPM12 and the ASLtbx toolbox (https://www.nitrc.org/projects/asltbx/). Preprocessing includes motion correction of the ASL time series, co-registration to the individual 3D-T1WI structural image, pairwise subtraction between labeled and control images to generate perfusion-weighted images, and quantitative CBF map calculation using the single-compartment model in accordance with the consensus recommendations (61). The CBF maps will then be spatially normalized to MNI space using the transformation parameters derived from the structural image normalization, resampled at 2 mm × 2 mm × 2 mm voxel size, and spatially smoothed with a 6 mm FWHM Gaussian kernel. Two-sample Student’s t-tests and paired Student’s t-tests will be conducted to examine the between-group and within-group differences in regional CBF, respectively. The results will be corrected by GRF Theory (voxel-level *P* < 0.005, cluster-level *P* < 0.05). Across all imaging modalities, these thresholds were applied to control the family-wise error rate; GRF correction was used for the voxel-wise analyses (rs-fMRI, VBM, and ASL), whereas the Monte Carlo cluster-wise method was adopted for the surface-based analyses (CT and CSA) because it is better suited to the geometry of the cortical surface. These criteria follow widely adopted neuroimaging conventions, balancing protection against false positives with sensitivity to true taVNS-related effects.

Additionally, Pearson’s correlation analyses will be performed to explore the relationships between changes in neuroimaging indicators (ALFF, fALFF, ReHo, FC, GMV, CT, CSA, and CBF) and changes in clinical outcome measures (PSQI, NIHSS, ADL, HAMD-17, and HAMA-14), with statistical significance set at *P* < 0.05 (Bonferroni-corrected). For these brain-behavior correlations, the mean values of each neuroimaging metric will first be extracted from the clusters showing significant between- or within-group differences in the preceding voxel- or vertex-wise analyses; these extracted values, rather than whole-brain maps, will then be correlated with the corresponding changes in clinical scale scores. Pearson’s correlation will be applied when both variables satisfy the assumptions of normality and linearity, and Spearman’s rank correlation will be used otherwise. The taVNS and sham-taVNS groups will be analyzed separately, and the Bonferroni method will be used to correct for the number of correlation tests performed.

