
#### Clinical data analysis

All data in this study will be analyzed using SPSS 26.0 software (IBM Corp., Armonk, NY, USA). Continuous data following a normal distribution are expressed as mean ± standard deviation (Mean ± SD). Intergroup comparisons will be performed using the independent samples t-test, while pre- and post-treatment comparisons within groups will be performed using the paired t-test. Continuous data not following a normal distribution are expressed as median and interquartile range [M(P25, P75)], and intergroup comparisons will be performed using the Mann-Whitney U test. For dynamic observational data involving multiple time points, repeated measures ANOVA will be used. Categorical data will be described using frequencies and percentages (%). Intergroup comparisons for ordinal categorical data will be performed using the chi-square (χ²) test or Fisher’s exact test, while for nominal categorical data, the Kruskal-Wallis H rank-sum test will be used. Furthermore, for the correlation between clinical symptom scales and multimodal MRI indices, Pearson or Spearman correlation analysis will be used, depending on whether the data meet the assumptions of normal distribution and linearity. All statistical tests will be two-sided, and *P* < 0.05 will be considered statistically significant.

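### The randomised contrast is principal for the imaging outcome but is not carried into the mechanism step, where within-arm changes are labelled taVNS-related and can feed the brain-behaviour correlations

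*Protocol article*

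**What the plan says.** All references are to the protocol article.

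- **Primary outcomes** ranks the contrasts: "the principal comparison is the between-group difference in these changes (taVNS vs. sham-taVNS), with within-group pre-to-post changes assessed as a secondary contrast". Secondary outcomes likewise names the between-group difference in change for each scale, alongside its time course.
- **Imaging data analysis, rs-fMRI** uses one phrase for the two-sample and paired tests together. They are to "examine the differences in taVNS-related central responses between groups and within groups". Connectivity seeds come from areas with significant ALFF, fALFF or ReHo differences, without saying from which contrast.
- **Imaging data analysis, correlation paragraph** takes the imaging values "extracted from the clusters showing significant between- or within-group differences in the preceding voxel- or vertex-wise analyses". It adds: "The taVNS and sham-taVNS groups will be analyzed separately". No comparison of the correlations between arms is described.
- **Basic treatment**: "all participants will receive standard basic treatment, including conventional post-stroke medication and rehabilitation training". **Interventions** explains the 4-week course partly by the wish "to align with the typical timescale of post-stroke neuroplastic change".
- **Discussion** expects the correlations to clarify the central mechanisms of taVNS. It also names candidate regions and directions of effect in advance.

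**The concern.** A paired test within one arm measures change over time. It cannot separate stimulation from whatever else happens in those 4 weeks; that is the purpose of the sham arm. The protocol respects this for the principal imaging comparison. It drops it where clusters are chosen for correlation, because the two contrasts are joined by a plain or.

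A cluster with no between-group effect therefore qualifies if it changed within the taVNS arm. Its change can then be correlated, in that arm alone, with the change in PSQI or another scale. If recovery or rehabilitation moves both quantities, the correlation is real but owes nothing to taVNS. Since the Introduction and Discussion present mechanism as a main purpose of the trial, the step that supports the mechanism statement should rest on the randomised comparison.

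Connectivity carries a related risk. It is one of the primary imaging indicators, and its seeds could be drawn from within-arm findings.

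**Working it through.** The protocol gives no figure for shared change, so there is nothing to reproduce. The check asks how the planned tests behave when taVNS has no effect and both arms change alike.

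**Inputs**
- n = 24 per arm (Sample size calculation).
- Two-sided P<0.05 (Clinical data analysis), and voxel-level P<0.005 (Imaging data analysis).
- Shared change d, in SD units of the change score: **assumed**, 0 to 0.8.

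**1. Paired test in the taVNS arm**

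The statistic is noncentral t with 23 degrees of freedom and noncentrality d × √24. Critical values are 2.069 for P<0.05 and 3.104 for P<0.005. For d = 0.5 the noncentrality is 0.5 × 4.899 = 2.449.

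| d (assumed) | Significant at P<0.05 | Significant at P<0.005, single voxel |
|---|---|---|
| 0 | 5% | 0.5% |
| 0.2 | 16% | 2.8% |
| 0.3 | 29% | 7.2% |
| 0.5 | 65% | 29% |
| 0.8 | 96% | 78% |

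The last column is for one voxel without the cluster step, so it is not a whole-brain error rate.

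**2. Between-group test on change scores**

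The expected difference is d − d = 0 whatever d is, so the test keeps its nominal level. Simulation (20,000 runs) gave 4.9% at d = 0.5 and 5.0% at d = 0.8 for P<0.05, and 0.5% in both cases for P<0.005.

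**3. Significant in taVNS but not in sham**

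With independent arms and no taVNS effect the chance is p(1 − p). At d = 0.5 this is 0.65 × 0.35 = 0.23; at d = 0.3 it is 0.29 × 0.71 = 0.21. Setting the two paired results side by side therefore does not replace the direct comparison.

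**4. Correlation within one arm**

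Suppose recovery alone links imaging change and clinical change at correlation r (**assumed**). For illustration, take a Bonferroni divisor of 8 metrics × 5 scales = 40.

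| r (assumed) | Significant at P<0.05 | Significant at P<0.05/40 |
|---|---|---|
| 0.3 | 30% | 3% |
| 0.5 | 73% | 23% |

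Bonferroni correction limits chance findings. It does not remove an association that exists for reasons other than taVNS.

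**The case against.** **The main inference is protected.** The between-group difference in change is principal for imaging and is named for every scale. This stands. A reader might infer that the primary comparison is compromised; it is not.

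**The label is one loose phrase.** The parallel sentences for structure and CBF are neutral, and nowhere does the protocol say that a within-arm change would be claimed as a taVNS effect after a null between-group result. This is fair as to the label. The cluster rule, however, is explicit.

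**The correlations are exploratory, corrected, and run in the sham arm too.** This stands and lowers the severity. The sham correlations would give an informal view of recovery-driven association, but no planned test uses them.

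**Within-arm change is not certain.** A reader might infer that the design guarantees it, or that patients enter 2 weeks after stroke. The documents support neither. The 2-week criterion concerns when insomnia first occurred, no upper limit on time since stroke is given, and the remark on the timescale of plasticity does not say that untreated patients will change. Shared change is plausible, no more.

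**Regression to the mean.** Entry requires "Pittsburgh Sleep Quality Index (PSQI) score > 7", so a reader might measure the problem by the expected fall in PSQI. With the Introduction's pooled mean of 8.12 for stroke survivors, and assumed SD 3.5–4.5 and retest correlation 0.70–0.87, that fall is 0.3–1.0 point. But participants must have post-stroke insomnia, so their reference mean is probably higher. At an assumed 11–12 with SD 3.5, the fall is only about 0.1–0.3 point. It also reaches MRI metrics only through their correlation with PSQI. It does not measure the imaging problem and is not relied on here.

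**Within-arm tests of the scales.** Under Clinical data analysis, "pre- and post-treatment comparisons within groups will be performed using the paired t-test". Ranked below a between-group comparison, such tests are not an error, and barring them would be largely a matter of preference.

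**Conclusion.** The point holds in limited form. The protocol places within-arm change under a taVNS label, admits clusters significant only within an arm to arm-specific correlations, and reads those correlations as mechanism. Shared change can therefore enter a mechanism statement without any randomised contrast. This is a rule that the protocol states, not a detail left to an analysis plan.

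The size depends on a shared change that the protocol does not give. At an assumed 0.5 SD with no taVNS effect, the paired test is significant in about 65% of trials and the between-group test in about 5%. Over assumed changes of 0.2 to 0.8 SD the paired figure runs from 16% to 96%.

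Severity is should-fix: the affected step is secondary and exploratory, and the principal between-group comparison is untouched.

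**What to change.** 1. **Imaging data analysis, rs-fMRI:** reserve the taVNS-related label for the between-group difference in change, and describe within-group results as change over time.
2. **Seeds and clusters:** take connectivity seeds and correlation clusters from the between-group difference in change, or from the candidate regions already named in the Discussion.
3. **Correlation step:** choosing clusters from the randomised contrast is not enough, because recovery can still drive a correlation within one arm. Before any mechanistic reading, test an arm-by-imaging-change interaction on clinical change in both arms together. Keep the arm-specific correlations as descriptive.

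**Cost:** wording only, with no extra patients, scans or visits. Fewer clusters may qualify, and the interaction test has low power. For an assumed correlation of 0.5 in one arm and 0 in the other, Fisher's z difference is 0.549 with standard error √(1/21 + 1/21) = 0.309. The ratio is 1.78, which gives about 43% power at two-sided P<0.05. A non-significant interaction should therefore be reported as inconclusive.

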The maintenance of the sleep-wake cycle depends on the dynamic balance at the whole-brain level, involving the precise regulation of specific neural circuits such as the thalamo-cortical loop and the reticular formation of the brainstem (20). After a stroke, ischemic injury directly disrupts these critical neuroanatomical structures and neurotransmitter pathways, leading to an imbalance between sleep drive and the arousal system (21). In recent years, with the rapid development of neuroimaging, multimodal Magnetic Resonance Imaging (MRI) technology has become a key tool for unraveling the complex neuropathological mechanisms of PSI. High-resolution T1-weighted imaging (3D-T1WI) serves as a cornerstone for assessing the integrity of brain microstructure. Techniques such as Voxel-Based Morphometry (VBM) and Surface-Based Morphometry (SBM) enable the precise quantification of key morphological indicators, including Gray Matter Volume (GMV), cortical thickness, and cortical surface area (22, 23). Previous studies have shown that chronic sleep deprivation not only leads to gray matter atrophy in brain regions related to cognition and emotion, such as the hippocampus, prefrontal cortex, and anterior cingulate cortex, but also induces widespread changes in the surface area of the sensorimotor cortex (24, 25). In PSI, these neurodegenerative changes secondary to insomnia, when superimposed on the primary stroke lesion, constitute the anatomical basis for the impeded recovery of neurological function in patients.

As an effective tool for investigating spontaneous neuronal activity by monitoring fluctuations in blood oxygen levels, resting-state functional MRI (rs-fMRI) helps assess the spontaneous evolution of Blood Oxygen Level-Dependent (BOLD) signals and abnormalities in functional connectivity within core brain regions regulating “emotion-arousal” in patients with PSI (26). Recent fMRI studies reveal that PSI is characterized by multi-dimensional spontaneous activity abnormalities, specifically within the visual processing cortex, sensorimotor cortex, and Default Mode Network (DMN) nodes (26). Furthermore, Arterial Spin Labeling (ASL) provides non-invasive, contrast-free quantification of Cerebral Blood Flow (CBF) (27). ASL effectively captures hypoperfusion in ischemic areas and sleep-related brain regions, thereby reflecting the degree of impairment in neurovascular coupling function (28).

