### Multimodal MRI data acquisition

All multimodal MRI data will be acquired on a Siemens 3.0T Vida scanner at the Shunyi Hospital of Beijing Hospital of Traditional Chinese Medicine. For each participant, scanning will be performed at two time points: on the day before the first treatment session and on the day after completing the 4-week intervention. To minimize variability, all scans will be obtained using identical hardware, sequences, and acquisition parameters at both time points.

Three sequences will be acquired in a fixed order. First, resting-state functional MRI (rs-fMRI) will be obtained using a gradient-echo echo-planar imaging (GRE-EPI) sequence to capture spontaneous neural activity. During the scan, participants will be instructed to remain awake with their eyes closed, stay as still as possible, and refrain from engaging in any structured thought. Next, a three-dimensional T1-weighted image (3D-T1WI) will be acquired to provide high-resolution structural information for morphometric analysis and for spatial normalization of the functional and perfusion data. Finally, arterial spin labeling (ASL) perfusion imaging will be performed to quantify cerebral blood flow. The detailed acquisition parameters for all three sequences are summarized in **Table 1**.

**Table 1 T1:** Acquisition parameters of the multimodal MRI sequences.

Parameter	rs-fMRI (GRE-EPI)	3D-T1WI	ASL
Repetition time, TR (ms)	2000	2530	4200
Echo time, TE (ms)	30	2.98	38.06
Flip angle, FA (°)	90	7	120
Field of view, FOV (mm)	224 × 224	256 × 256	224 × 224
Matrix	64 × 64	256 × 256	64 × 64
Slice thickness (mm)	3.5	1.0	3.5
Number of slices	32	192	46
Voxel size (mm³)	3.5 × 3.5 × 3.5	1.0 × 1.0 × 1.0	3.5 × 3.5 × 3.5
Number of time points	200	—	—
Acquisition time	6 min 46 s	6 min 3 s	7 min 21 s

rs-fMRI, resting-state functional MRI; GRE-EPI, gradient-echo echo-planar imaging; 3D-T1WI, three-dimensional T1-weighted imaging; ASL, arterial spin labeling; TR, repetition time; TE, echo time; FA, flip angle; FOV, field of view.

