Structural 3D-T1WI data processing will be performed using two complementary approaches. For VBM, the CAT12 toolbox (http://www.neuro.uni-jena.de/cat/) implemented in SPM12 will be employed. Data preprocessing includes bias-field correction, tissue segmentation into GM, White Matter (WM), and CSF maps, spatial normalization to Montreal Neurological Institute (MNI) space using the Diffeomorphic Anatomical Registration Through Exponentiated Lie Algebra (DARTEL) algorithm, modulation to preserve the total amount of tissue within each voxel, resampling at 1.5 mm × 1.5 mm × 1.5 mm voxel size, and spatial smoothing with an 8 mm Full-Width at Half Maximum (FWHM) Gaussian kernel. For SBM, cortical reconstruction and parcellation will be performed using FreeSurfer (ver. 7.2; https://surfer.nmr.mgh.harvard.edu/). The processing pipeline includes motion correction, intensity normalization, skull stripping, automated tissue segmentation, identification of the white matter and pial surfaces, cortical surface inflation and registration to a spherical atlas, and cortical parcellation based on the Desikan-Killiany atlas (59). CT will be computed as the shortest distance between the white matter and pial surfaces at each vertex, and cortical surface area (CSA) will be calculated as the total area of the cortical mantle at each vertex. Surface maps will be smoothed with a 10 mm FWHM Gaussian kernel. Two-sample Student’s t-tests and paired Student’s t-tests will be applied to examine inter-group and intra-group differences in GMV, CT, and CSA, respectively. VBM results will be corrected by GRF Theory (voxel-level *P* < 0.005, cluster-level *P* < 0.05), and SBM results will be corrected using the Monte Carlo cluster-wise correction method (cluster-forming threshold *P* < 0.001, cluster-level *P* < 0.05) (60).

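### The structural primary outcomes are 4-week changes in patients with infarcts, but the listed T1 steps neither link a patient's two scans nor handle the lesion

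*Protocol article*

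**What the plan says.** Under Primary outcomes: "The primary outcome is defined as the change in these multimodal MRI indicators from baseline to the end of the 4-week intervention". GMV, CT and CSA are among the indicators. The main contrast is the difference in change between arms; within-group change is a secondary contrast. Multimodal MRI data acquisition sets two scans per patient, "on the day before the first treatment session and on the day after completing the 4-week intervention".

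The first inclusion criterion is "Confirmed by MRI and meeting the diagnostic criteria for ischemic cerebrovascular disease". Neither the inclusion nor the exclusion criteria limit lesion size, site or side. The Introduction describes insomnia-related structural change "when superimposed on the primary stroke lesion".

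Imaging data analysis then lists the structural processing:

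- **VBM (CAT12):** "Data preprocessing includes bias-field correction, tissue segmentation into GM, White Matter (WM), and CSF maps", followed by "spatial normalization to Montreal Neurological Institute (MNI) space using the Diffeomorphic Anatomical Registration Through Exponentiated Lie Algebra (DARTEL) algorithm", modulation, resampling to 1.5 mm and 8 mm smoothing.
- **Surfaces (FreeSurfer 7.2):** "The processing pipeline includes motion correction, intensity normalization, skull stripping, automated tissue segmentation", followed by surface identification, spherical registration, parcellation and 10 mm smoothing.

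Both feed two-sample and paired t-tests. The ASL paragraph takes the CBF maps to MNI space with the parameters from the structural normalisation. The correlation paragraph extracts values from clusters that are significant between or within groups, and analyses the arms separately.

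**The concern.** A change score carries the processing error of two scans. If each scan is segmented, normalised and surface-reconstructed without reference to the other, the two errors are largely independent and both enter the difference. Linking the scans within the patient exists to reduce this, and the steps listed include nothing of the kind.

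The lesion is a second source of error. Automated segmentation can put infarcted tissue in the wrong class, and registration can distort around it. The Discussion predicts effects in the thalamus, prefrontal cortex, hippocampus and anterior cingulate, and nothing in the eligibility criteria keeps infarcts out of those regions. Because the CBF maps inherit the structural transform, a registration error there does not stay in the structural results.

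At stake are the precision of a primary comparison in a trial of 24 per arm, and the reading of within-group change and brain-behavior correlations as effects of stimulation.

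**Working it through.** **1. Set the outcome beside the steps.**

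| Needed for 4-week change in stroke patients | In Imaging data analysis? |
|---|---|
| Bias correction, segmentation, normalisation, smoothing | Yes, with software and kernel |
| Surface reconstruction, atlas | Yes, with version |
| Within-subject registration or template, or a longitudinal stream | Not named |
| Lesion mask, lesion option or exclusion of lesioned tissue | Not named, here or elsewhere |

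**2. Error in the change.** Let each scan have processing-error SD s, with correlation r between a patient's two errors. The error variance of the change is 2s²(1 − r). With independent errors (r = 0) this is 2s²; as r approaches 1 it vanishes. Within-subject processing aims to raise r. A stable lesion that is misread in the same way twice also has high r and partly cancels. A lesion that changes between scans does not.

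**3. How much scan-to-scan consistency matters.** The article states no effect size, SD, power or reliability. Its 24 per group comes from a recommended minimum of 12 plus an unquantified allowance for loss, so there is no power figure to reproduce. The rest of this step and step 4 is illustration under assumptions. With equal variance at both scans and correlation ρ between them, SD(change) = SD × √(2(1 − ρ)). For one test at two-sided 0.05 and 80% power (normal approximation), the detectable difference at 24 per arm is (1.960 + 0.842) × √(2/24) = 0.81 SD of change.

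| Assumed ρ | SD of change (cross-sectional SD = 1) | Detectable difference (cross-sectional SD) |
|---|---|---|
| 0.99 | 0.14 | 0.11 |
| 0.95 | 0.32 | 0.26 |
| 0.90 | 0.45 | 0.36 |
| 0.80 | 0.63 | 0.51 |

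A single test at 0.05 is not the planned analysis. At the planned cluster-forming thresholds, taken as two-sided, the same formula gives 1.05 SD of change at 0.005 (VBM) and 1.19 at 0.001 (surfaces). This still ignores cluster correction.

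**4. Cost of added noise.** Start from a difference with 80% power at 24 per arm and two-sided 0.05, and inflate the SD of change by an assumed factor f. The n per arm that restores 80% power is 24 × f², rounded up.

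| f | Power at 24 per arm | n per arm for 80% |
|---|---|---|
| 1.10 | 72% | 30 |
| 1.25 | 61% | 38 |
| 1.50 | 46% | 54 |
| 2.00 | 29% | 96 |

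The documents do not say which f, if any, applies here.

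**5. Which analyses are exposed.**

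- **Between-group change:** arms are randomised and processed alike, so the main effect is lost precision.
- **Paired within-group change:** no control arm enters the test, so lesion evolution, or processing error that shifts with it, can register as change.
- **Correlations:** these accept clusters from the within-group tests and run by arm, so they inherit that weakness.

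Insomnia must begin more than 2 weeks after the acute stroke, which leaves room for subacute infarcts that are still evolving over the next four weeks.

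**The case against.** The strongest reply is that single-scan processing is inferred. The article never says that the two scans are handled independently, both lists are introduced as inclusive, and segmentation, normalisation and surface reconstruction occur in longitudinal streams too. A journal article may leave stream settings and masking to a fuller document. This stands as a limit on the wording: a reader might infer that the sponsor has chosen cross-sectional processing, and the text does not establish that. It does not dispose of the point, because the article fixes software, voxel size, kernels and atlas, and an analyst who runs exactly those steps gets unlinked scans and unhandled lesions.

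The second reply is that stable lesion errors partly cancel in the change and randomisation protects the main contrast. That is right, and chance imbalance at 24 per arm is covered by the test's error rate. A reader might infer a systematic between-arm bias in favor of stimulation; the design does not support that. The protection does not reach the paired tests or the correlations fed by them. Excluding unstable or recurrent stroke reduces lesion evolution but does not remove it.

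The third concerns size. One could assume that longitudinal processing cuts the SD of change by 30% to 50% and equate this to 24/0.7² = 49 to 24/0.5² = 96 per arm. Nothing in the documents anchors those reductions, so that equivalence should not be used.

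**Conclusion.** The point holds as a weakness in the specified pipeline that should be corrected; no error in results has been shown. The steps as listed do not match an outcome defined as within-patient change in patients with infarcts. The consequence is a risk of avoidable noise, felt as lost precision in the between-group comparison, and a risk that errors around evolving lesions appear as change in the paired tests and the correlations built on within-group clusters. Reuse of the structural normalisation extends the registration part of that risk to CBF.

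The gain cannot be sized: no reliability, SD of change or lesion-error figure is given. The tables show only that precision depends strongly on scan-to-scan consistency. The conclusion assumes that the listed steps would be run as written and that some lesions are still changing during the four weeks.

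**What to change.** In Imaging data analysis, before unblinding:

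1. State that both T1 scans are processed with the longitudinal streams of the software already named: CAT12 longitudinal for GMV, and FreeSurfer longitudinal with a within-subject template for CT and CSA.
2. In the ASL paragraph, use the same within-subject transform to MNI space at both time points.
3. Handle the lesion in segmentation and normalisation, with one baseline mask per patient or the toolbox's lesion option, prepared blind to arm.
4. Add a sensitivity analysis that excludes lesioned tissue, and say in advance how differing numbers of patients per voxel or vertex enter the t-tests and cluster correction.

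The cost is more computing time and up to 48 masks. Table 1 lists no dedicated lesion sequence, so masks may have to rely on the T1 image or the diagnostic MRI, and their quality should be reported. No extra patients are needed.
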